#### Self-report systemic health measures

##### Health-related quality of life

The EORTC Quality of Life-C30 [20] will assess health-related quality of life. Respondents will report on functioning (including physical, cognitive and emotional), and presenting symptoms (e.g., fatigue, pain, nausea and vomiting, sleep disturbance, appetite, etc.). On items 1–28, respondents will indicate agreement on a 4-point Likert scale ranging from 1(Not at all) to 4(very Much). Items 29 and 30 utilize a 7-point Likert scale ranging from 1(very poor) to 7(excellent). Example items include *“Do you have trouble taking a long walk?”* and “*During the past week, were you limited in doing either you work or other daily activities?”.*

##### Health behaviors

Dietary intake (including sugar-sweetened beverages [SSBs]), alcohol use, and smoking behaviors will be assessed using items from the widely-utilized Behavioral Risk Factor Surveillance Survey [21]. On dietary intake items, respondents will indicate their consumption of vegetables, fruits and fiber/whole grains. Item ratings include less than once/week; once per week, 2–3 times per week, 4–6 times per week, once/day, and more than once per day. Respondents will also indicate their daily meal patterns (i.e., average number consumed, and meal skipping). An example item includes: “*How often did you eat a green leafy or lettuce salad, with or without other vegetables?”.* Sugar-sweetened beverage consumption will be captured via 3 items, which assess consumption of SSB in past 7 days, average daily consumption, and knowledge of health implications of frequent consumption of SSBs. On alcohol use items, respondents will indicate number of alcoholic drinks consumed across lifespan, and within past 30 days. Item ratings include: 0 days, 1 or 2 days, 3–5 days, 3–9 days, 10–19 days, 20–29 days, and all 30 days. Lastly, smoking behaviors will be assessed via 4 items, which assess smoking behaviors across lifespan, daily smoking behaviors, and daily number of cigarettes consumed. Item ratings are similar to those of alcohol use.

##### Clinical characteristics

Participants will report cancer treatment history via 11 items, which assess cancer type, treatment, and overall cancer care. Participants will also indicate the presence of prior or existing health conditions (oral and systemic) including but not limited to: diabetes, stroke, lung disease, stomach ulcers, bleeding gums, sensitive teeth, etc.

### Participant timeline {13}(Table 2)

**Table 2 Tab2:**
[figure not shown]
Schedule of enrollment, intervention and assessments for FLOSS Project

### Sample size {14}

A power analysis was conducted using effect sizes for telehealth-delivered, psycho-behavioral interventions in cancer survivors. A 6-month study by Abrahams et al. (2017) examining the efficacy of an internet-based cognitive behavior therapy intervention for breast cancer survivors reported mean quality of life of 77.1 (SD = 16.5) and 63.9 (SD = 20.1) for intervention arm and care as usual arm, respectively. This translates to an effect size (standardized mean difference) of 0.71 standard deviations. Based on this finding, we determine sample size for selected power levels and the standardized mean difference (Cohen’s *d*) between the telehealth and usual care arms of the study in the neighborhood of 0.71 standard deviations. Table 3 below presents sample sizes per arm required for selected values of Cohen’s *d* at level of significance, α = 0.05.

**Table 3 Tab3:** Sample sizes per group for selected power and effect size

Power	Effect size (Standardized mean difference)					
	0.30	0.40	0.50	0.60	0.70	0.80
80%	175	99	64	45	33	26
90%	234	132	85	59	44	34

For this study, we will recruit 100 subjects (50 subjects per arm) and expect to detect a medium effect size of approximately 0.60 standard deviations (Cohen’s *d* = 0.60) with 80% power, allowing for an attrition rate of 10%. Of note, sample size will not be adjusted during this trial. Results from this trial will help determine sample size for a larger trial.

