### Outcomes {12}

#### Primary outcomes

Primary outcomes of interest are related to oral health, including image-rated oral mucositis image-rated gingival inflammation and quality of life. We will also capture self-reported oral mucositis and gingival inflammation via survey (using Qualtrics Online Survey Platform [18]). Our target endpoint is 6-months, post-randomization.

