#### Secondary outcomes

Secondary outcomes of interest are related to systemic health and include systemic inflammation, overall quality of life, and comorbidities. Measures include collection of biospecimen, anthropometrics, and self-report measures. The target endpoint for secondary measures is 6-months, post-randomization.

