## Statistical methods

### Statistical methods for primary and secondary outcomes {20a}

Demographic and other baseline data including cancer-related clinical characteristics will be listed and summarized descriptively by intervention arm (THI and UC). Categorical data will be presented as frequencies and percentages. For continuous data, mean, standard deviation, median, minimum, and maximum will be presented. For selected parameters, 25th and 75th percentiles will also be presented.

Intention to treat (ITT) analysis will be performed for all participants who enrolled and randomly allocated to one of the clinical trials arms. Descriptive statistics will be used to summarize the original scores for the outcomes (oral and systemic health outcomes), as well as change from baseline, at each scheduled assessment timepoint for the THI and UC group. Additionally, change from baseline in the scale and subscale values at the time of each assessment will be summarized. Participants with an evaluable baseline score and at least one evaluable post baseline score during the treatment period will be included in the change from baseline analyses. The significance of the difference in mean scores between the two arms will be assessed using paired t-test or Wilcoxon signed-rank test. In addition, for each outcome measure, analysis of covariance (ANCOVA) models will be fit to evaluate the difference in mean scores at each timepoint post-baseline with baseline scores as concomitant variables. Repeated measures ANOVA models will be used to examine mean differences in the scores of image-rated oral mucositis, image rated gum inflammation, blood biomarkers of systemic inflammation, and oral and overall quality of life between the THI and UC arms. The differences in least square means between the treatment arms and corresponding 95% confidence interval at selected timepoints will be presented. The Bonferroni method will be used to adjust models for multiple testing.

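### The 80% power at d = 0.60 is for a single test at alpha 0.05, while the plan has three primary outcomes and a Bonferroni adjustment

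*Protocol article*

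**What the plan says.** Three statements in the protocol article bear on this point.

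- **Sample size {14}.** The per-arm numbers in Table 3 are given "at level of significance, α = 0.05". With 100 participants, 50 per arm, the authors "expect to detect a medium effect size of approximately 0.60 standard deviations" with 80% power after 10% attrition. Multiplicity is not mentioned.
- **Primary outcomes, under Outcomes {12}.** The primary outcomes relate to oral health, "including image-rated oral mucositis image-rated gingival inflammation and quality of life", with 6 months as the target endpoint. None is singled out as the lead. The section on oral health-related quality of life then lists two instruments, the OHIP-14 and the EORTC oral health module.
- **Statistical methods {20a}.** After describing t-tests or rank tests, ANCOVA with the baseline score as covariate, and repeated measures models, the section ends: "The Bonferroni method will be used to adjust models for multiple testing". It does not say which tests form the family.

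**The concern.** A power figure belongs to a test at a particular significance level. Bonferroni over k tests runs each at 0.05/k, so a trial sized for one test at 0.05 has less power per test than stated unless the calculation allowed for k. With three primary outcomes and no lead, a family that covers them has at least three members.

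What is at stake is how the result is read. The protocol says the sample size will not be adjusted during the trial. A non-significant primary outcome would be taken as coming from a test with an 80% chance of detecting 0.60 SD, when the adjusted test may have had a clearly smaller chance.

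**Working it through.** **Inputs.** From Sample size {14}: d = 0.60, alpha = 0.05, power 80%, 50 per arm, attrition 10%, hence 50 × 0.9 = 45 evaluable per arm. Sidedness is not stated. I take two-sided, because Table 3 reproduces on that basis. From Primary outcomes: three outcomes, or four tests if both oral quality-of-life instruments are tested. From Statistical methods {20a}: Bonferroni, alpha/k per test.

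**Step 1: reproduce the plan's figure.** Normal approximation: n = 2(z₁₋α/₂ + z₁₋β)²/d² = 2(1.960 + 0.842)²/0.36 = 43.6, so 44 per arm. The exact noncentral t calculation gives 44.59, so 45 per arm, and 45/0.9 = 50. Power at 45 per arm is 80.4%. The 12 cells of Table 3 match the t-test solutions rounded to the nearest integer (for d = 0.30 to 0.80 at 80% power: 175.38, 99.08, 63.77, 44.59, 33.02, 25.52). The stated figure is therefore the unadjusted single-test calculation, with no hidden allowance.

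**Step 2: the same calculation at alpha/k.** The noncentrality is d√(n/2) = 0.60 × √22.5 = 2.846, with 88 degrees of freedom. A normal approximation to power is Φ(2.846 − z₁₋α/₂ₖ). For k = 3 that is Φ(2.846 − 2.394) = Φ(0.452) = 67.4%. The exact t-test values are:

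| Tests in family (k) | Alpha per test | Power per outcome, d = 0.60, 45 per arm | d detectable at 80% power | Completers per arm for 80% at d = 0.60 |
|---|---|---|---|---|
| 1 | 0.0500 | 80.4% | 0.60 | 45 |
| 2 | 0.0250 | 71.4% | 0.66 | 55 |
| 3 | 0.0167 | 65.7% | 0.69 | 60 |
| 4 | 0.0125 | 61.7% | 0.72 | 64 |

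With 10% attrition, 60 completers means 60/0.9 = 66.7, so 67 per arm (134 in all); 64 means 64/0.9 = 71.1, so 72 per arm (144). With no attrition at all (50 per arm), power at d = 0.60 is 76.4%, 71.3% and 67.5% for k = 2, 3 and 4.

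**Step 3: what baseline adjustment could recover.** If the score correlates r with its baseline, ANCOVA acts roughly as if the effect were d/√(1 − r²). The protocol gives no r, so these are assumptions:

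| Assumed r | Effective d | Power, k = 3 | Power, k = 4 |
|---|---|---|---|
| 0.3 | 0.60/√0.91 = 0.629 | 71% | 67% |
| 0.5 | 0.60/√0.75 = 0.693 | 80% | 77% |
| 0.6 | 0.60/√0.64 = 0.750 | 87% | 84% |

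**Step 4: power at the cited effect.** At d = 0.71, the effect taken from the cited study, unadjusted t-test power with 45 per arm is 82.1% for k = 3 and 79.1% for k = 4.

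**The case against.** The strongest reply is that no single lower figure can be called the trial's power. Most of it stands.

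- **The family is undefined.** The Bonferroni sentence directly follows one about differences at selected timepoints. It could mean adjustment within each model over 6 and 12 months, which is k = 2 and 71%. A family that took in secondary outcomes would give less than 62%, but the protocol supplies no count. A detailed family may also sit in an analysis plan that is not shown. None of this rescues the stated figure: on the protocol's own t-test basis, every family of two or more falls short of 80%.
- **The planned analysis includes ANCOVA.** Step 3 shows that a baseline correlation near 0.5 would restore about 80% for k = 3. The sample size section claims no such gain, so this is a reason to state the assumption rather than evidence that the claim holds.
- **The figures are per outcome.** The chance of success on at least one of three outcomes, each with d = 0.60 at 0.0167, is higher: 1 − (1 − 0.657)³ = 96% if they are independent, and by simulation about 88% at a between-outcome correlation of 0.5 and 82 to 83% at 0.7. The protocol does not define its power that way.
- **Power at 0.71 stays near 80%.** True, but the stated target is 0.60.

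A reader might also infer that the planning effect concerns only a secondary outcome, since the cited study reported quality of life and the secondary list reads "Secondary outcomes of interest are related to systemic health and include systemic inflammation, overall quality of life, and comorbidities". The documents do not support that. The primary list names quality of life without qualification, and the sample size section does not say which instrument the cited study used.

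**Conclusion.** The point holds as a mismatch between sections. The arithmetic in the sample size section is right for one test, but the power it states does not carry over to a Bonferroni-adjusted analysis of three primary outcomes. On the protocol's own basis (two-sided, two-sample t-test, 45 evaluable per arm, d = 0.60), the loss against 80.4% is about 9 percentage points for k = 2, 15 for k = 3 and 19 for k = 4. For k = 3 or 4 the effect detectable with 80% power moves to about the size of the cited 0.71, so the margin from planning at 0.60 is largely used up.

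A reader might go further and conclude that the trial's actual power is 62 to 66%. That does not follow: the range assumes k = 3 or 4, success judged per outcome, and no gain from baseline adjustment, and the documents fix none of the three. Nor does it follow that the sample size was miscalculated or that more participants must be recruited.

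**What to change.** 1. In Statistical methods {20a}, define the Bonferroni family as the primary outcomes at 6 months, and say whether oral health-related quality of life contributes one test or two.
2. In Sample size {14}, restate the power at the adjusted alpha. Possible text: *With 45 evaluable per arm and Bonferroni over three (four) primary tests, the trial has 80% power per outcome for d = 0.69 (0.72) and about 66% (62%) for d = 0.60, before any gain from baseline adjustment.*
3. If ANCOVA is relied on to reach 80%, state the assumed baseline correlation and its basis.

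Holm's procedure in place of Bonferroni would keep the same error control and is never less powerful; it is an optional gain. Naming one lead outcome at 0.05, with the others in a fixed sequence, would also make the single-test calculation apply to that outcome, but that is a design choice and not a correction.

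The cost is a text change, with no added participants. The stated power becomes less favourable. Since recruitment was due to start in May 2024, the change should be a documented amendment made before outcomes are examined by arm.

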### Recruitment {15}

Participants will be actively recruited from community settings. Study personnel will recruit through the organizational networks of community partners (e.g., survivorship and cancer support organizations, newsletters, flyers advertisements) and targeted outreach in the Washington Metropolitan area. Community partners will aid recruitment by directing eligible participants (as indicated on study promotional materials) to online screener form or study coordinator via telephone. Prospective participants will also be identified through cancer survivorship groups and research registries. Individuals who preliminarily meet eligibility criteria will be contacted via phone or email by study personnel.

## Assignment of interventions: allocation

### Sequence generation {16a}

Following completion of baseline assessments, participants will be randomly assigned, in a 1:1 ratio, to either the THI or UC arm. A computer-based randomization sequence will be generated by the first author. Intervention allocations will be placed in a password protected folder and stored electronically on university-approved servers (i.e., Box). The study coordinator will examine the randomization allocation on the day of the consent visit and inform participants of their group allocation at the conclusion of their baseline visits and assign participants to group based on these numbers.

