### Who will take informed consent? {26a}

Trained research personnel, including a postdoctoral research fellow and graduate students will obtain informed consent from potential trial participants.

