### Concealment mechanism {16b}

Intervention allocations (identified by study ID numbers) will be entered into a document and placed in a password protected folder and stored electronically on university-approved servers (i.e., Box).

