### Implementation {16c}

The study coordinator and trained research assistants will enroll participants. The study coordinator will verbally inform participants of their intervention allocation following baseline assessments.

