## Assignment of interventions: blinding

### Who will be blinded {17a}

The study PI and data analysts will be blinded after assignment to interventions.

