## Oversight and monitoring

### Composition of the coordinating centre and trial steering committee {5d}

The Trial Steering Committee consists of a postdoctoral fellow who acts as a study coordinator and co-investigator; 3–4 graduate-level research assistants, and 2 clinical personnel (phlebotomist, exercise physiologist).

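### Allocation is not adequately concealed from enrolling staff: the coordinator who enrols also opens the ID-linked allocation document on the consent day, with no rule that consent and baseline be finished first

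*Protocol article*

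**What the plan says.** The procedure is spread over several sections of the protocol article.

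- **Generation.** Sequence generation {16a}: "A computer-based randomization sequence will be generated by the first author".
- **Storage.** Concealment mechanism {16b}: "Intervention allocations (identified by study ID numbers) will be entered into a document and placed in a password protected folder". The rest of that section says only that the folder is on a university server.
- **Time of assignment.** Sequence generation {16a} opens: "Following completion of baseline assessments, participants will be randomly assigned, in a 1:1 ratio, to either the THI or UC arm".
- **Look-up.** The same section continues: "The study coordinator will examine the randomization allocation on the day of the consent visit". Participants are told their arm only when the baseline visits end.
- **Enrolment.** Implementation {16c}: "The study coordinator and trained research assistants will enroll participants".
- **Who the coordinator is.** Composition of the coordinating centre and trial steering committee {5d} describes "a postdoctoral fellow who acts as a study coordinator and co-investigator". The section on informed consent {26a} names a postdoctoral research fellow among those who obtain consent.
- **Blinding.** Who will be blinded {17a}: "The study PI and data analysts will be blinded after assignment to interventions". The coordinator and the assessors are not named.

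**The concern.** Allocation concealment means that whoever decides whether and when a person enters the trial cannot know the arm that person will get. Here the coordinator holds both roles. A password keeps outsiders away from the list, but does not conceal it from someone whose task is to open it. The text delays what the participant is told, not what the coordinator knows.

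Two routes to bias follow. Staff who know an upcoming arm can, without intending to, encourage, defer or discourage a candidate according to apparent motivation or oral condition. The coordinator is also a telephone contact for prospective participants (Recruitment {15}), so this could begin before the visit. Second, knowledge of the arm during the baseline visit can influence how intraoral images and body measurements are taken.

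With 100 participants and primary outcomes that rest on image ratings and self-report, the randomised comparison depends on closing both routes. They cannot be closed in retrospect for people already enrolled.

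**Working it through.** **1. The passages side by side**

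| Question | Protocol article | Consequence |
|---|---|---|
| Who enrols? | Coordinator and research assistants (Implementation {16c}) | The coordinator influences entry |
| Who reads the allocation? | Coordinator (Sequence generation {16a}) | Same person |
| When? | Day of the consent visit (Sequence generation {16a}) | Order relative to signature and baseline is not fixed |
| What is read? | One document of allocations by study ID (Concealment mechanism {16b}) | No limit to a single participant is stated |
| What stops foreknowledge? | Password-protected folder (Concealment mechanism {16b}) | No barrier to the person who opens it |
| Is the coordinator blinded? | Only the PI and analysts are named (Who will be blinded {17a}) | No later safeguard |

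No section describes sealed envelopes, a central service, a third-party holder or release of one allocation at a time.

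**2. The plan's own figure, for context**

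Sample size {14} gives 45 per arm in Table 3 for d = 0.60 at 80% power, and recruits 50 per arm. The two-sample t-test at two-sided α = 0.05 requires 44.59, hence 45. Allowing for 10% attrition, 45 / (1 − 0.10) = 50 per arm. Power with 45 per arm is 80.4%. The sample size reproduces and does not depend on concealment.

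**3. Illustration of what a residual shift would do**

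Inputs: n = 45 evaluable per arm (Sample size {14}); two-sided α = 0.05 (the article gives 0.05, and the two-sided reading reproduces Table 3); a spurious difference of b SD between arms with no true effect. **The values of b are assumptions; the documents give none.**

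Non-centrality: λ = b × √(n/2) = b × √22.5 = 4.743 b.
Critical value: t(0.975; 88 df) = 1.987.
False-positive rate: P(|T| > 1.987), where T is non-central t with 88 df and parameter λ.

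| Assumed b (SD) | λ | False-positive rate |
|---|---|---|
| 0 | 0 | 5.0% |
| 0.1 | 0.474 | 7.6% |
| 0.2 | 0.949 | 15.5% |
| 0.3 | 1.423 | 29.1% |

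This is one unadjusted test. The plan also has ANCOVA on baseline scores and a Bonferroni correction (Statistical methods {20a}), so b should be read as the part of the shift left after baseline adjustment. The article does not say how many tests the correction covers. If it were three (an assumption), α = 0.05/3 = 0.0167, the critical value is 2.441, and shifts of 0.2 and 0.3 SD give about 7% and 16% against a nominal 1.7%. The absolute rates fall, but the inflation relative to nominal remains.

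**The case against.** The strongest reply concerns timing. The article does not say that the look-up comes before the consent signature or before baseline ends. If consent and baseline fall on one day, a look-up at the end of that day fits the statement that assignment follows baseline. A reader might therefore infer a flat contradiction within Sequence generation {16a}, or that the coordinator certainly knows the arm during baseline; the text supports neither. What stands is that no safe order is fixed, and that even a late look-up for one participant could show later assignments.

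A reader might also infer that every future allocation is known to everyone who enrols. The article describes neither the layout of the document nor how IDs are issued, and it does not say that the research assistants have access. Sight of later assignments is a fair inference from a single ID-linked document, and it applies to the coordinator.

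The baseline route has limits. Participants learn their arm only afterwards, so their questionnaires are not coloured by it. The images are reviewed by a dental consultant who is not said to see the list. The exposure that remains is in the capture of images and in anthropometry.

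ANCOVA does help, since it removes imbalance carried by the measured baseline score. It does not remove differences in unmeasured traits such as motivation, and it is weakened if the baseline measurement was itself influenced.

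Finally, generation of the sequence by the first author invites the inference that PI blinding is void or that the enroller made the list. The document does not establish who the first author is, and generation by an author is not a flaw in itself. This is a query only.

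It cannot be said that the detail is simply left to a fuller document: the article states a procedure under all three allocation items, and the weakness lies in that procedure.

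**Conclusion.** The concern holds in this form: followed as written, the procedure does not adequately conceal allocation from the coordinator who enrols, so selection at entry and influence on baseline image capture and anthropometry are possible. It rests on the stated overlap of enrolling and reading the list, on the absence of any fixed order, and on the absence of one-at-a-time release. It does not show that bias has occurred.

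The size is unknown. The rates of about 8%, 16% and 29% are conditional on assumed residual shifts of 0.1, 0.2 and 0.3 SD and on an unadjusted test; they are not this plan's error rates. The point should be fixed all the same, because concealment underpins the randomised comparison and the planned analysis can repair only the part carried by baseline scores.

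**What to change.** For participants still to be enrolled (Trial status gives June 2026 as the end of recruitment):

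1. Replace the unused part of the list. Have the new part generated and held by an existing person with no role in enrolment, intervention delivery, assessment or blinded analysis. Someone on the blinded analysis team would not do, because the data analysts are to remain blinded.
2. Release one allocation at a time, electronically or by sequentially numbered opaque sealed envelopes, only after consent is signed and all baseline data and images are saved.
3. Remove enrolling staff's access to the list.
4. In Sequence generation {16a}, replace the look-up on the consent day with this order, and state the release method under Concealment mechanism {16b}.

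As a query, ask the investigators to confirm that the first author who generates the sequence is neither the PI, who is to be blinded, nor the enrolling coordinator.

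The cost is minor set-up and a short amendment. Sample size is unchanged. Participants already enrolled are not affected by the change, and the report should say under which procedure each group was allocated.
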